## Abstract

**Background:**

Refugees are at high risk for developing mental illnesses. Due to language and cultural barriers, there is need for specifically adapted therapeutic procedures for refugees in inpatient mental health care settings. Internet-based applications in refugee mother tongues have the potential to improve the outcomes of mental health care for this vulnerable population. The key research question of the present implementation study is whether the newly developed “blended ALMAMAR” app for Arabic and Farsi speaking refugees in Germany is used and accepted by patients and professionals in routine inpatient mental health care (blended care).

**Methods:**

We present the design of an observational, prospective multicenter implementation study in eight psychiatric hospitals. We plan to recruit 100 Farsi or Arabic speaking refugees receiving in-patient treatment due to depression, anxiety disorder, posttraumatic stress disorder or substance use disorders. These patients will get access to the “blended ALMAMAR” app during their inpatient stay in a blended-care approach. We will assess the usage (e.g., duration and frequency of use of the app) as well as subjective acceptability and usability of the intervention. To identify sociodemographic and clinical factors associated with “blended ALMAMAR” usage, we will also perform clinical and questionnaire assessments.

**Discussion:**

The newly developed “blended ALMAMAR” app may help to close communication gaps for the hard-to reach and vulnerable group of refugees in inpatient mental health care. It is the first blended-care intervention that addresses severely mentally ill refugees in an inpatient psychiatric setting in Germany.

**Trial registration:**

The trial was registered in the German Clinical Trials Register on November 11, 2021 (DRKS00025972) and adapted on November 14, 2023.

## Background

The number of refugees and asylum applicants in Europe and Germany remains high (approximately 1 million refugees from the Ukraine and more than 217.000 first applications for asylum in 2022 in Germany). People from Arabic- and Farsi-speaking countries (e.g., Syria, Afghanistan, Iraq, Iran) are among those who submitted the highest number of asylum applications in Germany [1]. Refugees are at a high risk for developing mental illnesses due to the burden of pre-, peri- and postmigration stressors [2, 3]. The prevalence of posttraumatic stress disorder (PTSD) among refugees is approximately 30% and there is an equally high prevalence of depression [4–7]. Accordingly, the high number of refugees from different countries is a challenge for European mental health care systems [e.g. 2] and there is a need to implement effective mental healthcare approaches [8]. Treatment methods and support services need to be adapted to the specific needs of refugee populations [9]. Internet-based applications have the potential to improve the outcomes of mental healthcare for refugees by providing culturally sensitive, cost-effective, native-language services [9].

Numerous studies have demonstrated beneficial effects of stand-alone internet-based interventions *and* blended online interventions in combination with face-to-face psychotherapy in non-refugee populations. A systematic review of 44 blended care studies for outpatient treatment for mental disorders in adult populations suggested that blended care approaches were clinically effective [10]. To date, three studies implemented internet-based applications in psychiatric inpatient settings in Germany and reported promising results for (non-refugee) patients with depression [11–13].

Refugees now represent a large group in inpatient mental healthcare [14]. However, language and cultural factors are major barriers to the delivery and uptake of mental health services: participation in group therapies is difficult, specific therapeutic programs are lacking, and, finally, the use of professional translators or language mediators is not possible 24/7 and involves extra administrative and organisational effort and costs for the healthcare providers. Elements of blended therapy in mother tongue may help clinicians to use time more effectively, increase adherence and maintain changes achieved during face-to-face psychotherapy [10]. Blended care approaches via smartphones may be particularly promising since the majority of refugees use smartphones to access the internet every day [15].

Two recent international implementation studies in Belgium [16] and Canada [17] emphasized hindering factors regarding the implementation process of internet-based applications in inpatient mental healthcare settings. Professionals mentioned high patient turnover in the acute inpatient setting [16], lack of time and a high workload for professionals, technical difficulties and insufficient structural facilities for the use of e-mental health as barriers [17]. Insufficient staff qualification, lack of training and supervision, and other organizational and administrative factors may also hinder the clinical implementation of internet-based applications [18]. The potential of internet-based support in inpatient mental healthcare has therefore not been fully utilized. Guided support by health professionals leading to patient recruitment and stabilizing program adherence as well as professional qualification, training and supervision of practitioners seem to be crucial. The process of adapting and implementing apps for inpatient mental healthcare needs to address clinicians, patients and administrative staff [19]. To date, many clinical practitioners in inpatient settings still lack practical experience with e-mental health care [20]. The gap between the development of effective e-mental health treatments for mental disorders and service provision in routine mental healthcare is considerable. Implementation research is aimed at closing this gap [21].

### Study objectives

The key research question of the present study is whether the newly developed “blended ALMAMAR” app can be successfully implemented in routine clinical inpatient mental healthcare for Arabic- and Farsi-speaking refugees, and whether the app will be accepted and used by patients and professionals. Furthermore, we aim to identify facilitators and barriers to implementation.

## Methods

### Trial design and study setting

This study is part of the I-REACH consortium (**I**nternet-based **Re**fugee ment**a**l **h**ealth **C**are) [https://www.mentalhealth4refugees.de/en/i-reach], which aims to develop and test culturally and contextually adapted internet-based interventions for Arabic- and Farsi-speaking refugees in in- and outpatient settings in Germany. The consortium is funded by a grant from the German Federal Ministry of Education and Research (BMBF) (FKZ: 01EF1806C). This study (subproject 4 of the I-REACH project) focuses on the implementation of blended care using an app in inpatient routine mental healthcare of the psychiatric clinics of the Rhineland Regional Council (Landschaftsverband Rheinland, LVR). The LVR is the largest provider of inpatient mental health care in the Rhineland region. LVR operates nine public psychiatric hospitals, serves 4.5 million inhabitants with a total of 3403 inpatient beds (as of 2020). We chose a routine inpatient setting to ascertain the transferability of the study findings to “real world” mental healthcare. The study is designed as an observational, quasi-experimental, prospective multicenter implementation study. Eight of the nine LVR-clinics participate as recruitment centers in this study and receive case fees for the recruitment and data collection of the patients. The Section Health Services Research at the LVR-Institute for Research and Education is responsible for coordinating the study.

### Inclusion and exclusion criteria

Patients are included based on the following inclusion criteria: (a) adult age (≥ 18 years old), (b) Arabic- or Farsi-speaking refugees, (c) current inpatient mental healthcare in one of the participating LVR-clinics due to depression (codes F32-F34 of the International Classification of Diseases (ICD), tenth revision), anxiety disorder (F40, F41), trauma related disorders (F43) or substance use disorders (F10-F19), and d) written informed consent. Key exclusion criteria are (a) (health) conditions precluding the use of internet-based applications such as blindness, analphabetism, severe intellectual impairment, or (b) involuntary inpatient stay. All refugee patients admitted voluntarily for inpatient mental healthcare for the aforementioned mental disorders are screened for participation.

### Recruitment, participant timeline and informed consent

The recruitment phase started in June 2022 and is planned for 31 months (until December 2024). Physicians and psychologists who work as therapists in the wards and day-clinics of the eight LVR hospitals can participate in the study as treatment providers for the “blended ALMAMAR” app (“therapists”). To familiarize therapists with the app “blended ALMAMAR”, a training course for therapists (two hours) was developed. Having participated successfully in this course, therapists obtain access to the app by an individual account. Therapists recruit patients during inpatient stay (see Fig. 1). Patients can be recruited shortly after admission or at some later point during their inpatient stay. After checking the inclusion and exclusion criteria, therapists hand out study information to suitable participants. A demo version of the “blended ALMAMAR” app can be shown for illustration if needed. Written informed consent sheets are available in Arabic, Farsi and German and interpreters can be consulted. Within the informed consent process, patients will be asked whether they agree to be contacted in case of dropout for participation in an ancillary study of the I-REACH consortium which examines reasons for dropout (“Prediction and prevention of dropout in research, diagnostics, and treatment with refugees”; PrevDrop). In case of consent, a separate informed consent is obtained by the participant for their participation in a qualitative interview. After written informed consent has been obtained, therapists give patients access to the “blended ALMAMAR” app to use it in addition to routine care (i.e., a setting blended of smartphone and personal contacts). All participants of the study fill out standardized questionnaires in Arabic or Farsi at study inclusion (t0: baseline assessment), upon discharge from inpatient treatment (t1: post assessment), and six months after discharge (t2: follow-up assessment). There is no predefined length of participation in the study since the duration of inpatient stay may vary largely between patients. At t0 and t1, questionnaires are delivered via the app. Follow-up assessments (t2) are conducted by telephone or via video call by the therapist (if necessary, with the help of an interpreter). In order to ascertain a high call back rate, therapists note the contact details of patients at discharge and can already fix a date for the planned interview.

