### Assessments and outcomes

The main hypothesis of the study is that the “blended ALMAMAR” app can be successfully implemented in inpatient psychiatric-psychotherapeutic care of refugees, and that it is accepted and used by therapists and patients.

The *primary endpoint* will be the use of the “blended ALMAMAR” app during inpatient stay, measured by:

recruitment rate (proportion of eligible patients who signed a consent form to participate);app usage rate (proportion of recruited patients who use the app at least once);average number of modules completed in the app;average duration and frequency of use of the app.

*Secondary endpoints* are clinical assessments, as well as acceptability and usability of the intervention. These will be assessed using questionnaire data from patients and therapists at each of the three time points (baseline assessment at study entry t0, post assessment at discharge t1, and follow-up six months after discharge t2; see Table 2 for an overview of all assessments).

**Table 2 Tab2:** Overview of the planned assessments

	Instrument	Who fills in?	Timepoint of measurement			Estimated duration (minutes)
No.			T0: Baseline (Admission)	T1: Post (Discharge)	T2: Follow-up (six months after discharge)	
1	Sociodemographic data	Patient	x			10
2	User rating of the app (CSQ-8) [30]	Patient		x	x	5
3	Post Migration Living Difficulties Checklist (PMLD) [26]	Patient	x			10
4	Expectation of therapy	Patient	x			5
5	EQ-5D-5 L (Health-related quality of life) [27]	Patient	x	x	x	5
6	*Health care utilization [selected questions from FIMA* [28] *and FIMPsy* [29]:					
	Number and specialisation of outpatient physician contacts in the last six months before inpatient admission (or baseline) and in the six months after discharge	Patient	x		x	3
	Number of inpatient stays and treatment days in the last six months before inpatient admission (or baseline) and in the six months after discharge	Patient	x		x	3
	Diagnoses, medications	Patient	x		x	3
	Number of visits to emergency departments in the last six months before hospitalization (or baseline) and in the six months after discharge	Patient	x		x	1
	Current employment [yes/no]	Patient	x		x	3
7	Main diagnosis of mental disorder and secondary diagnosis(es)	Therapist	x	x		1
8	Number of inpatient psychiatric treatment days and stays in the last six and twelve months, respectively	Therapist	x	x	x	3
9	Symptom severity (CGI) [31] and functional ability (GAF) [32]	Therapist	x	x		5

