10	Regular insurance status [yes/no]	Therapist	x			1
11	Assessment of therapy success [rating 1–5]	Therapist		x		1

At baseline, patients fill out questionnaires on post-migration stressors (27-items post-migration living difficulties checklist (PMLD); [26]), expectations for the current therapy (3 items; self-developed questionnaire), and health-related quality of life (EQ-5D-5 L; [27]). Additionally, we assess costs of health care utilization by selected questions from the FIMA [28] and FIMPsy [29] questionnaires by asking about the number of physician contacts and inpatient stays within the last six months before admission/baseline and about the duration of these inpatient stays, past diagnoses, medication and current employment status. Asylum-related factors (e.g. length of stay, asylum status) are assessed at baseline. At discharge, patients fill in a user rating of the app (adapted version of the CSQ-8; [30]) as well as the health-related quality of life (EQ-5D-5 L; [27]).

Therapists will indicate the current main diagnosis of mental disorders as well as secondary diagnoses. In addition, they will perform clinical ratings of symptom severity (CGI; [31]) and functional ability (GAF; [32]) at each assessment. They will indicate the number of inpatient psychiatric treatment days (at post-assessment) and perform a rating of overall therapy success at discharge (rating 1–5). In case of dropout, therapists document reasons. In a separate assessment, therapists will be asked about their attitudes/expectations and experiences with digital interventions before working with the app (pre-assessment) and after approximately 12–24 months of experience with the app (post-assessment). For this assessment, we created short questionnaires that are given to all therapists after an initial app training session.

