### Statistical methods for primary and secondary outcomes

Descriptive statistics will be performed for all quantitative variables at t0, t1 and t2. For all categorical variables, numerical and frequency data will be calculated. The main outcome variables (recruitment rate, app usage rate, average number of modules completed in the app, average duration and frequency of use of the app) are descriptive data that can be analysed by recruitment documentation of the clinics as well as log-in data from the app. Regarding secondary outcome variables, we will perform pre-post analyses regarding CGI and GAF as well as health-related quality of life using Wilcoxon test. Intention-to-treat (ITT) and per protocol analysis will be conducted to avoid selective reporting and biases in the analyses. Missing values will be imputed by the appropriate statistical methods depending on the type of missing. FIMA und FIMPsy will be used to measure healthcare utilization which will be multiplied with unit costs to calculate costs. Using these costs, a budget impact analysis will be conducted to analyse the cost impact of introducing “blended ALMAMAR” into routine care.

Subgroup analyses will be performed (e.g. regarding diagnoses and provider location), and predictors and mediators (e.g. PMLD or health-related quality of life scores) will be included as covariates. SPSS software will be used for data analyses and two-sided p-values of p < .05 will be accepted as statistically significant.

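### t0 moves with the day of enrolment and app access ends at discharge, so relating t0 severity scores to total app use can create or mask an association unless both times are accounted for

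*Protocol article*

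**What the plan says.** All references are to the protocol article.

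- **Enrolment.** *Recruitment, participant timeline and informed consent* sets no window after admission: "Patients can be recruited shortly after admission or at some later point during their inpatient stay". The same section places the questionnaires "at study inclusion (t0: baseline assessment), upon discharge from inpatient treatment (t1: post assessment"), so t0 moves with enrolment. Participation has no fixed length because stays vary.
- **Label.** In Table 2 the t0 column heading reads "T0: Baseline (Admission").
- **State scores at t0.** Table 2 lists EQ-5D-5L, therapy expectation, CGI and GAF at t0. For the therapist ratings the text says "they will perform clinical ratings of symptom severity (CGI; [31]) and functional ability (GAF; [32]) at each assessment".
- **End of access.** *Adaptations from the original CETA* says the app works only during the inpatient stay and is deactivated at discharge.
- **Usage.** Besides the recruitment rate and the proportion who use the app at least once, *Assessments and outcomes* defines use as "average number of modules completed in the app;average duration and frequency of use of the app". No denominator of days with access is given.
- **Aim.** The abstract states: "To identify sociodemographic and clinical factors associated with “blended ALMAMAR” usage, we will also perform clinical and questionnaire assessments".
- **Covariates.** *Statistical methods for primary and secondary outcomes* says that "predictors and mediators (e.g. PMLD or health-related quality of life scores) will be included as covariates". Enrolment day and days of access are not among the examples. Quality of life, which is, is itself a score that moves with enrolment day.

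**The concern.** Enrolment day can act on both sides of the analysis of clinical factors. In a stay of given length, a later enrolment means more routine treatment before t0, and so a milder score if the patient is recovering. It also means fewer days left with the app. When the t0 score is set against total use, low severity and low use then occur together because of timing.

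Two wrong answers become possible. One is that sicker patients use the app more, when severity plays no part. The other is that a real hindrance from severe illness goes unseen, although the study wants to find barriers to implementation. Therapy expectation rated well into the stay may likewise partly reflect experience.

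**Working it through.** The article gives no distribution of enrolment day, length of stay, recovery or usage, so there is no stated figure to reproduce. Taken from the documents: n = 100, 20% dropout (100 × 0.80 = 80), two-sided 0.05. Everything else below is an assumption.

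**1. The mechanism in one line.** Let L be the length of stay, E the days from admission to t0, A the admission severity in SD units, r the recovery over the full stay and u the use per day.

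- t0 score = A − r × E/L
- total use = u × (L − E)

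Take two patients with A = 0, r = 1 and L = 28. Enrolled at admission: score 0, access 28 days, total 28u. Enrolled at 60% of the stay (E = 16.8): score −0.6, access 11.2 days, total 11.2u. Severity has no effect on use, yet the milder score goes with 40% of the total. Per day of access, both give u.

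**2. Size under no true effect.** Assumed: median stay 28 days (log SD 0.4); enrolment uniform over the first part of the stay; rating error 0.3 SD; overdispersed use counts proportional to days left; Spearman test of t0 score against total use; 1,500 runs per scenario. Monte Carlo error at a true 5% is √(0.05 × 0.95/1500) = 0.6 points.

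False-positive rate, n = 100 (mean correlation in brackets):

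| Enrolment spread over | r = 0.5 SD | r = 1 SD | r = 2 SD |
|---|---|---|---|
| admission only | 5.3% (0.00) | 5.3% (0.00) | 4.7% (0.01) |
| first 30% | 5.0% (0.00) | 4.1% (0.00) | 4.9% (0.02) |
| first 60% | 4.5% (0.02) | 6.7% (0.04) | 11.3% (0.07) |
| first 90% | 8.7% (0.06) | 17.5% (0.11) | 51.4% (0.20) |

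With n = 80 the last row is 7.4%, 16.8% and 41.8%.

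**3. Both halves are needed.** With no recovery the rate is about 5% at every spread. With recovery of 1 or 2 SD over the 90% window, but days left made independent of enrolment time, it is 5.2% and 4.1%.

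**4. Sensitivity to assumptions.** A separate simulation, also on assumed inputs, gave 9%, 23% and 65% for the same recoveries in the 90% window, and about 5% to 10% with enrolment in the first half or earlier. A third took a mean stay of 42 days, admission CGI with SD 0.8 and improvement of 1.0 to 2.0 points (1.0/0.8 = 1.25 to 2.0/0.8 = 2.5 SD). It gave 44% to 92% in the 90% window and 8% to 13% in the first half. Direction and pattern agree; the level does not.

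**5. Masking.** With a similar set-up to step 2, a true log-rate slope of −0.3 per SD of admission severity and 1,000 runs, the effect is detected from total use in:

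- about 70% of studies if all enrol at admission;
- 57% (r = 1) and 47% (r = 2) with enrolment over the first half;
- 21% and 5% with enrolment over 90%.

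**6. What repairs it.** In the step 2 simulation, use per day of access brings false positives to 3.5–6.3% in all scenarios (mean correlation at most 0.03). Adjusting for enrolment day and days left gives 3.8–6.1%. In the masking case, joint adjustment restores detection to 65–74%. In the worst scenario (90%, r = 2), use per day alone reaches 48% against 65%.

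Enrolment day alone is not enough. Take A = 0, r = 1 and E = 7. A 28-day stay gives score −7/28 = −0.25 and 21 days of access; a 42-day stay gives −7/42 = −0.17 and 35 days. At the same enrolment day, the higher score still has more access.

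**The case against.** **An analysis plan may handle this.** The covariates are introduced as examples, the article is condensed and no SAP is shown, so it cannot be said that timing will be ignored. That stands. What remains is that a floating t0 and usage without an access denominator are both stated in the article, and related as they stand they can mislead.

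**It is only a denominator problem.** Use per day of access removes nearly all of the false link. This also stands, and the fix relies on it. It does not make t0 scores from different days mean the same thing, which is why detection of a true effect in the widest case is better when enrolment day is adjusted for as well.

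**The Table 2 label is editorial.** The sentence introducing the table places t0 at study entry, and the utilisation rows distinguish admission from baseline. Agreed: the label needs reconciling but carries little of the weight.

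**The scope is narrow.** The study is about feasibility, the primary endpoint is descriptive, and the factor aim is stated in the abstract rather than under *Study objectives*. All true, and this limits the point to state scores in a secondary analysis.

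**Conclusion.** The concern holds as a conditional one. If t0 state scores (CGI, GAF, EQ-5D-5L, possibly therapy expectation) are related to total use, enrolment timing can create a spurious positive association with severity or mask a true negative one. False positives are negligible to small, about 4% to 11%, when enrolment falls in roughly the first half of the stay. Even there, the masking run loses 70 − 57 = 13 to 70 − 47 = 23 points of detection. With enrolment over nearly the whole stay and substantial recovery, the distortion can be large. All of this rests on assumed stay, recovery and usage models.

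Three stronger readings are tempting and not supported:

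- **Recovery alone produces the false link.** It does not; shrinking access and an analysis of totals are also required (step 3).
- **The aim is certain to get a biased answer.** The documents do not show how late patients enrol or how much they recover.
- **The whole factor analysis or the primary endpoint is undermined.** Sociodemographic factors and diagnosis do not shift with enrolment day in this way, and the primary endpoint does not rest on this association.

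**What to change.** 1. Derive for each patient the days from admission to t0 and the days of app access (t0 to discharge).
2. In every analysis relating a t0 state score to usage, analyse use per day of access, or enter access days as an offset or covariate, and also adjust for days from admission to t0. Adjusting for enrolment day alone does not suffice.
3. Add a sensitivity analysis in patients enrolled early in the stay, with the cut-off fixed beforehand (for example 7 days).
4. Reconcile the t0 heading in Table 2 with the recruitment section by calling it study inclusion.
5. Report the distribution of days from admission to t0, so that readers can judge how far the problem applies.

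The cost is one or two extra covariates in about 100 patients. The dates must be retrievable: the article mentions logged actions and recorded treatment days but no admission-date field, so clinic records may be needed. The analysis then describes intensity of use while the app was available rather than total use, and should be reported in those terms.
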